### Strategies to improve adherence to interventions {11c}

To prevent visit deviation and ensure that the investigational product can be administered within the approved period, the research staff will contact the subjects to inform them of the visit date in advance (2 weeks, 1 week, 1 day). Upon receiving consent for participation, investigators should try to obtain at least two or more contact points to stay in touch with the subjects. In addition, as ALS patients are at high risk of accidents (e.g. fall, aspiration) due to carelessness, so investigators shall thoroughly conduct safety education to subjects and guardians to prevent accidents.

### Relevant concomitant care permitted or prohibited during the trial {11d}

All participants will receive a standard dose of riluzole except for side effects, and symptomatic treatments are also allowed in all groups.

The following medication will be permitted concomitantly administered during this trial.Any medication taken by a subject before their participation in this clinical trial and is considered not to affect the interpretation of these study results can be allowed as determined by the investigator.Any medicinal products transiently used to treat other diseases or adverse events can be allowed after consulting with the investigator.

The following medications that may interfere with the outcome of this trial will be prohibited during this trial.Yoo solution (ursodeoxycholic acid) for treatment of ALSRadicava® (edaravone)Any stem cell products except for LenzumestrocelOther Investigational products indicated for ALS treatmentHerbal medicines (such medicines are not completely characterized and may cause toxic effects or unexpected drug interactions that can adversely affect the efficacy and safety evaluation)Nuedexta® (dextromethorphan and quinidine)Ketas® (Ibudilast)

If concomitant medication is necessary for the medical treatment of a subject, as determined by the investigator or a medical doctor, the medicine may be used during the clinical study period (from lead-in period L-V1).

### Provisions for post-trial care {30}

To provide direct benefit from the investigational drug, participants who are allocated to the control group will receive Lenzumestrocel after the primary endpoint (at 13 and 14 months after the first administration).

In compliance with the compensation criteria for subjects, the sponsor should keep the subjects compensated for any injury that occurred either by an adverse event, investigational products, or treatment that attributes directly to the investigational products.

### Outcomes {12}

The two primary endpoints are a joint-rank test of function (ALS Functional Rating Scale-Revised) and overall survival (Table 1). The joint-rank test is a robust endpoint for ALS studies because of the ability to interpret death and functional change [18].

**Table 1 Tab1:** Description of primary, secondary, exploratory endpoints and analysis method

Endpoints	Description	Analysis method
Primary	(1) Difference in joint rank scores between study Group 2 and control group at 12 months (2) Difference in joint rank scores between study Group 1 and control group at 6 months	(1, 2) Analysis of covariance (ANCOVA) with adjustment of baseline ALSFRS-R score, baseline ALSFRS-R progression rate, and stratification factors (1, 2) Generalized Gehan-Wilcoxon rank test for supportive analysis
Secondary	(1) Difference in joint rank scores between study Group 2 and control group at 6 months (2) Change from baseline in ALSFRS-R score at 12 months (study Group 2 and control group) (3) Change from baseline in ALSFRS-R score at 6 months (study Group 1 and control group)	(1, 2, 3) ANCOVA with adjustment of baseline ALSFRS-R score, baseline ALSFRS-R progression rate, and stratification factors
	(4) Time-to-event at 12 months (study Group 2 and control group) (5) Time-to-event at 6 months (study Group 1 and control group)	(4, 5) Stratified cox proportional hazards model with adjustment of baseline ALSFRS-R progression rate and stratification factors
Exploratory	(1) Comparison of the change from baseline in SVC score at 6 months (study Group 1 and control group) and 12 months (study Group 2 and control group)	(1, 3, 8, 10) ANCOVA with adjustment of the baseline value, baseline ALSFRS-R progression rate, and stratification factors
	(2) Change from baseline in SVC score at 36 months (3) Comparison of the change from baseline in muscular strength at 6 months (study Group 1 and control group) and 12 months (study Group 2 and control group) (4) Change from baseline in muscular strength at 36 months (5) Time-to-event at 36 months (6) Comparison of the time-to-death at 6 months (study Group 1 and control group) and 12 months (study Group 2 and control group) (7) Time-to-death at 36 months (8) Comparison of the change from baseline in EQ-5D-5 L index value at 6 months (study Group 1 and control group) and 12 months (study Group 2 and control group) (9) Change from baseline in EQ-5D-5 L index value at 36 months (10) Comparison of the change from baseline in ALS Assessment Questionnaire (ALSAQ)-40 scores at 6 months (study Group 1 and control group) and 12 months (study Group 2 and control group) (11) Change from baseline in ALSAQ-40 scores at 36 months (12) Comparative analysis of cytokines in peripheral blood at baseline and individual points (13) Comparative analysis of cytokines in cerebrospinal at baseline and individual points (14) Analysis of regulatory T cell functions at baseline and individual points (15) Comparative analysis of transcriptome at baseline and individual points	(2, 4, 5, 7, 9, 11) Summarized by treatment groups
		(6) Stratified cox proportional hazards model with adjustment of baseline ALSFRS-R progression rate and stratification factors
		(12, 13, 14) Repeated measures generalized estimating equations with an AR(1) correlation structure
		(15) Standard transcriptome analysis pipeline

The first primary endpoint will be analysed at 6 months, comparing study Group 1 to the control group. The second primary outcome will be analysed at 12 months, comparing study Group 2 to the control group. The ALSFRS-R score (48 [normal] to 0 [maximally impaired]) will be assessed throughout a 3-month lead-in period and 12-month follow-up period, as shown in Fig. 1.

Secondary endpoints are a joint rank test at 6 months comparing study Group 2 to the control group, change from baseline in ALSFRS-R score at 6 months (comparing study Group 1 to control group), and again at 12 months (comparing study Group 2 to control group) (Table 1). Additional secondary endpoints are the time-to-event at 6 and 12 months.

The time until physical death or tracheostomy is recognized as an event where the disease progression functionally stops or the chronic use of a ventilator (chronic assisted ventilation; use of noninvasive ventilation for more than 20 h a day for 30 consecutive days or more), whichever comes earlier, subjects are observed for 6 months and 12 months after randomization.

Exploratory endpoints are listed in Table 1.

### Participant timeline {13}

Participant timeline is shown in Additional file 1.

### Sample size {14}

Sample size was calculated based on the previous phase I/II clinical trial (Table 2). Two hypotheses employed in this clinical study are as follows:

**Table 2 Tab2:** CAFS results (mean and standard deviation) at 6 and 12 months in phase I/II clinical trials

Point	Group	*N*	CAFS, mean	CAFS, SD
6 months	Study group	39	40.79	17.52
	Control group	27	22.96	16.56
12 months	Study group	39	39.14	18.22
	Control group	27	25.35	17.82

Hypothesis 1.*P*(uc_6_ < ut_6_) = 0.5 vs. *P*(uc_6_ < ut_6_) ≠ 0.5

Hypothesis 2.*P*(uc_12_ < ut_12_) = 0.5 vs. *P*(uc_12_ < ut_12_) ≠ 0.5

where

μc_6_: control group’s mean CAFS at 6 months

μt_6_: study Group 1’s mean CAFS at 6 months

μc_12_: control group’s mean CAFS at 1s2 months

μt_12_: study Group 2’s mean CAFS at 12 months

Accordingly, 1:1 of study Group 1 and control group, a two-sided significance level of 0.05 and statistical power of 80% were assumed for Hypothesis 1, and 1:1 of study Group 2 and control group, a two-sided significance level of 0.05 and statistical power of 80% were assumed for Hypothesis 2. For each hypothesis, the minimum number of subjects required to demonstrate that the study group showed superior results to the control group was calculated according to the following equation:

$$N=\frac{{\left({Z}_{\alpha }+{Z}_{\beta}\right)}^2}{12c\left(1-c\right){\left(p"-\frac{1}{2}\right)}^2}$$

two-sided significance level (α) = 0.05

statistical power (1-β) = 0.80

c = ratio of subjects in the study group relative to all subjects = 0.5

$$p"=\Pr \left({\mathrm{uc}}_{\mathrm{m}}<{\mathrm{ut}}_{\mathrm{m}}\right) if\ m= 12, 0.705; m= 6, 0.769$$

Based on the CAFS data obtained in phase I/II clinical trials, the number of subjects was calculated for two hypotheses to demonstrate the study group's superiority to the control group at 6 and 12 months. Table 3 shows the estimated sample size of this clinical study. For Hypothesis 1, the calculated number of subjects in study Group 1 is 19, and the calculated number of subjects in the control group is 19. For Hypothesis 2, the calculated number of subjects in study Group 2 is 32, and the estimated number of participants in the control group is 32. Since a single control group was used for both study Group 1 and study Group 2 in this clinical study, a larger number of subjects (32) in the control group for two hypotheses was selected. In conclusion, the minimum number of subjects required for this clinical study was 19 for study Group 1, 32 for study Group 2, and 32 for the control group. Considering the 15% (around) dropout rate, the number of subjects was increased to 23 for study Group 1, 38 for study Group 2, and 38 for the control group. However, to satisfy the stratified block randomization, a randomization ratio was generated at 1:2:2 for each group. Therefore, to satisfy the ratio of 1:2:2, 23 subjects in study Group 1, 46 subjects in study Group 2, and 46 subjects in the control group will be enrolled (115 subjects in total).

**Table 3 Tab3:** Estimated sample size considering dropout rate

	Study Group 1	Study Group 2	Control group	Total No. of subjects
Cases for efficacy evaluation	19	32	32	83
Cases including dropouts (approximately 15%)	23	46	46	115

### Recruitment {15}

We will promote the trial progress to Korean ALS associations and provide trial information to physicians who care for ALS patients to guide patients interested in the trial to transfer to the investigational site. The investigators at each site will faithfully perform the participant screening. Externally, we continue to promote the clinical trial by recruiting participants who meet the qualifications for the clinical study. Participants are given a detailed explanation of the clinical trial and enough time to consider participating in the clinical trial. Administrators continuously communicate with the trial participants and faithfully address any questions or opinions.

## Assignment of interventions: allocation

### Sequence generation {16a}

Randomization will be conducted by the stratified block randomization method (in consideration of stratification factors; Riluzole administration (Y or N) and ALS type (bulbar or limb)) to ensure that subjects are randomly assigned to study Group 1, study Group 2, and the control group at a ratio of 1:2:2. Randomization numbers are generated by an independent statistician of this clinical study using SAS (version 9.4 or higher, SAS Institute, Cary, NC, USA).

Subjects enrolled in the clinical study and satisfying the inclusion/exclusion criteria will be sequentially assigned to individual groups through the web-based automatic response service (Interactive Web Response System, IWRS) according to their randomization numbers. Such randomization numbers are used as subject identification codes during the clinical study period.

### Concealment mechanism {16b}

The randomization number generated through IWRS is e-mailed to the delegated staff, including investigators. The randomization number is sequenced so that the allocation information cannot be known, and therefore, no one knows the participants’ intervention arm. The unblinded staff who will be limitedly delegated to know the allocation information must access and check the RTSM (randomization and trial supply management) system.

The generation of the allocation sequence will be conducted by an independent statistician who is not involved in other clinical trial procedures. The investigators will enrol the participants.

## Assignment of interventions: blinding

### Who will be blinded {17a}

During the study period, the investigators, the study participants, all study site personnel (except for the site-specific unblinded staff in charge of storage, management, and administration of the investigational products), and data management personnel who will be involved in data cleaning and analysis of the data will be blinded to the treatment group assignment. Treatment unblinding for the study will occur after all clinical data have been received, data inconsistencies have been resolved, and the database is locked, except for safety reasons on a case-by-case basis (e.g. emergency unblinding).

### Procedure for unblinding if needed {17b}

Premature breaking of the blind will be allowed only if the subject’s well-being requires knowledge of the treatment allocation. Every attempt will be made to maintain blindness throughout the study.

In the event of an urgent safety issue where the randomized treatment of a subject is necessary to manage and treat the affected study subject (e.g. unblinding subjects due to SAEs that meet “expedited criteria” and require reporting to regulatory authorities), emergency unblinding is unavoidable. The principal investigator may consult with the sponsor. However, the principal investigator may perform code-breaking at their discretion if such consultation is not available or in an urgent situation.

The reason for unblinding must be recorded. However, the investigator must not record the subject treatment assignment in the study documentation and must not reveal the subject treatment assignment.

## Data collection and management

### Plans for assessment and collection of outcomes {18a}

Efficacy data (i.e. ALSFRS-R, SVC, FVC, and HHD) will be collected by blinded research staff who are certified after rater training. Data will be collected and managed via the Medidata Rave electronic data capture (EDC) system. Sites oversee data input on the EDC system.

### Plans to promote participant retention and complete follow-up {18b}

There are several alerting systems to keep the planned assessment or procedure schedule. The investigational product order system developed for the study will send a text to the research staff 1 week and 1 day before the planned date to contact the participants to remind them of their schedule. In addition, participants will repeatedly receive the reminder texts through the alerting system of each site at a set time before the planned schedule. Remote evaluation (ALSFRS-R, time-to-event/death, ALSAQ-40, and EQ-5D-5 L) can be conducted for subjects who do not withdraw their consent even though the clinical study is discontinued.

### Data management {19}

Investigators will conduct assessments and record them in the source data. Designated research staff will transcribe the data from source data into EDCs. We have delegated a series of processes related to data management to the CRO (clinical research organization) and reviewed these processes as a sponsor. Review and cleaning of data entered in EDC will be performed by CDA (Clinical Data Analyst). The potential data errors identified by triggered edit checks will prompt CDA to perform data-cleaning activities such as generating queries to a site.

Data review will be performed by study CDAs using the following documents:The Data Validation Specification (DVS): The document defines the programmed checks applied to the clinical data within the EDC.CRF Completion Instruction (CCI): This document provides the study investigators and the site staff with general guidelines for accessing and completing eCRFs. CCI describes the specific requirements used for completing paper CRFs and entering data into electronic CRFs.Offline Listing Mock shell: This document provides the manual view of study data via SAS listings and reports.Data Acquisition and Entry Specification: This document provides detailed information on handling other paper components received from the site for data entry into EDC.

### Confidentiality {27}

The sponsor shall identify the subjects in encrypted ID numbers for confidentiality; in ways, the name of subjects is not exposed in any data provided to it. Subjects’ medical information obtained during the clinical trial is confidential. Unless otherwise legally permitted or requested, such information may only be provided to third persons in ways permitted under (either) an informed consent form (or subjects' consent for use and publication of personal health information). However, such medical information may from time to time be provided to medical practitioners treating the subject or to any other medical practitioners deemed appropriate.

If requested, the clinical trial results may be provided to the persons in charge of local or international health authorities, monitors, staff, and assistants from the sponsor and the site IRBs for investigation purposes.

Plans for collection, laboratory evaluation, and storage of biological specimens for genetic or molecular analysis in this trial/future use {33}

Laboratory tests will be conducted at the clinical laboratory at each site according to the clinical study schedule for all subjects to evaluate overall health conditions. In addition, pregnancy tests and laboratory tests will be conducted before the administration of investigational products to verify the entire satisfaction of the inclusion/exclusion criteria. Laboratory tests for screening conducted at P-V0 (haematological tests, blood chemistry tests, urinalysis, blood coagulation tests) may be re-examined once based on the investigator's decision. Subject eligibility will be evaluated following the final examination results. Subjects who satisfy the inclusion and exclusion criteria at L-V1, L-V2, and P-V0 will be randomly assigned. This will be followed by the collection of bone marrow, according to the predetermined methods at P-V1.

In addition, to prepare the investigational products, CSF will be collected 1~2 days before administering investigational products. The bone marrow and CSF of subjects who have signed informed consent forms for human-derived materials can be stored for years, or as long as the subject wants, to improve quality control and research.

A study of biomarkers deemed necessary by the investigator may be conducted in addition to tests on clinical study schedules. Genetic testing samples for the ALS-related genes (*SOD1*, *TDP-43*, and *C9ORF72*) are submitted to the external central laboratory. Tests on blood and CSF samples for exploratory biological markers will be conducted only for those who gave informed consent in advance for additional research. Moreover, if the subject signed the informed consent form for human-derived materials, the remaining specimen can be stored for further study.

## Statistical methods

### Statistical methods for primary and secondary outcomes {20a}

All inferential statistical analyses will be based on a two-sided test with a type I error rate of 0.05.

The two primary efficacy endpoints for this study are as follows:Joint rank test using CAFS between study Group 2 and the control group at 12 monthsJoint rank test using CAFS between study Group 1 and the control group at 6 months

To protect the type I error rate for testing the two hypotheses, a hierarchical test procedure will be used. The hypotheses will be tested in the following order:

1.

H_0_: No difference between study Group 2 and the control group at 12 months.

H_1_: There is a difference between study Group 2 and the control group at 12 months.

2.

H_0_: No difference between study Group 1 and the control group at 6 months

H_1_: There is a difference between study Group 1 and the control group at 6 months.

If the first null hypothesis is rejected at an alpha level of 0.05, then study success is claimed. Next, the second null hypothesis is tested at an alpha level of 0.05. If the first null hypothesis is not rejected at an alpha level of 0.05, then the study fails.

At individual points, the differences between the study and control groups will be evaluated by analysis of covariance (ANCOVA) with covariate adjustment of baseline ALSFRS-R score, ALSFRS-R score progression rate, and stratification factors. When a 95% two-sided confidence interval for differences in mean joint rank scores between the study and control groups at each point does not comprise 0, it is considered that the study group's results are superior to those of the control group.

Additionally, for the primary efficacy endpoints, a generalized Gehan-Wilcoxon rank test will be used to compare CAFS between study groups and control groups as a supportive analysis.

The secondary efficacy endpoints for this study are as follows:Joint rank test using CAFS between study Group 2 and the control group at 6 monthsChange in ALSFRS-R score from baseline between study Group 2 and the control group at 12 monthsChange in ALSFRS-R score from baseline between study Group 1 and the control group at 6 monthsComparison of the time to an event at 6 months between study Group 1 and the control groupComparison of the time-to-event at 12 months between study Group 2 and the control group

The joint rank test is calculated in the same way as the primary outcome. The effect of the treatment in terms of the change from baseline in ALSFRS-R scores will be analysed using ANCOVA with covariate adjustment of baseline ALSFRS-R score, baseline ALSFRS-R score progression rate, and stratification factors. The effect of treatment in terms of time-to-event will be analysed using the stratified Cox proportional hazard model with covariate adjustment of baseline ALSFRS-R progression rate and stratification factors.

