## Introduction

### Background and rationale {6a}

Amyotrophic lateral sclerosis (ALS), which is known as Lou Gehrig’s disease, is a neurodegenerative disease characterized by progressive loss of selective motor neurons in the brain, brain stem, and spinal cord, which leads to progressive weakness with a fatal outcome due to paralyzed respiratory muscles within a mean of 2–4 years after diagnosis [1, 2]. Riluzole and edaravone are the only approved drugs by the Food and Drug Administration (FDA) with modest treatment effects on ALS progression [3, 4]. While the pathogenic mechanisms of sporadic ALS cases remain unknown, genetic mutations linked to the disease have provided a more accessible target for therapeutic development [5]. The development of therapies that specifically target known ALS mutations, including *chromosome 9 open reading frame 72* (*C9orf72*) and *superoxide dismutase 1* (*SOD1*), *fused in sarcoma* (*FUS*), has been rapidly evolving in recent years [6–8]. Despite the emerging precision of medicine in the genetic cause of ALS, more than 90~95% of patients present with sporadic ALS, and their clinical manifestations are more heterogeneous [9]. Lessons from previous failed trials focused on a single molecular target have led us to develop a therapeutic strategy aimed at multiple targets related to non-cell-autonomous toxicity.

Mesenchymal stem cell (MSC) therapy is a promising therapeutic strategy for addressing this issue. MSCs have been shown to exert diverse effects, such as stimulating intrinsic neurogenesis, releasing diverse neurotrophic factors, and modulating immunoinflammatory processes [10–13].

Lenzumestrocel (Korean product name; Neuronata-R® inj.) is an autologous bone marrow-derived mesenchymal stem cell and was designated as an orphan drug for concomitant therapy with riluzole in patients with ALS under the Revised Rule of Orphan Drug Designation by the Korea Ministry of Food and Drug Safety (Dec 31, 2013, MFDS Announcement No. 2013-262). In a previous phase II clinical trial, two repeated treatments with intrathecal autologous BM-MSCs (26-day interval) showed a therapeutic benefit lasting only 6 months, with good safety, in patients with ALS [14].

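### The primary joint-rank ANCOVA omits baseline slow vital capacity, which the trial already collects; adding it is a low-cost efficiency option of unknown, probably small, gain

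*Protocol article*

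**What the plan says.** The section on statistical methods for primary and secondary outcomes (item 20a) specifies "analysis of covariance (ANCOVA) with covariate adjustment of baseline ALSFRS-R score, ALSFRS-R score progression rate, and stratification factors" for the joint rank scores. Table 1 gives the same list for both primary comparisons, for the secondary joint rank comparison at 6 months, and for the two secondary comparisons of ALSFRS-R change. The stratification factors are riluzole use and ALS type (items 8 and 16a).

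SVC is measured in the trial: "Efficacy data (i.e. ALSFRS-R, SVC, FVC, and HHD) will be collected by blinded research staff" (item 18a). A baseline value is implied by the first exploratory endpoint in Table 1, "Comparison of the change from baseline in SVC score at 6 months", whose model is "ANCOVA with adjustment of the baseline value, baseline ALSFRS-R progression rate, and stratification factors". No primary or secondary model uses baseline SVC.

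Two places in the protocol make SVC plausibly prognostic. The background describes "a fatal outcome due to paralyzed respiratory muscles". The Discussion lists FVC, next to ALSFRS-R progression rate and disease onset, among variables that other trials have used for prognostic or predictive enrichment.

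**The concern.** The primary endpoint combines survival with functional change. If respiratory function at entry predicts who dies or declines faster, beyond what ALSFRS-R score, progression rate and ALS type already capture, then leaving it out keeps avoidable noise in the treatment comparison. Chance imbalance in SVC would also go uncorrected, because SVC is not a stratification factor.

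Precision matters most for the 12-month comparison of Group 2 with control. It is tested first, and if it misses the 0.05 level the study fails and the 6-month hypothesis is not tested. The planning effect for that test comes from 39 vs 27 patients in phase I/II, and the Discussion warns that dropout over 12 months may be higher than expected.

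**Working it through.** **Inputs from the protocol (items 14 and 20a).** Two-sided alpha 0.05, power 80%, c = 0.5, p'' = 0.705 at 12 months and 0.769 at 6 months; 19, 32 and 32 evaluable; about 15% dropout; 23, 46 and 46 enrolled.

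**Input not in the documents.** The partial R² of baseline SVC with the joint rank score, given the planned covariates. It is assumed below.

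**Step 1: reproduce the plan.** N = (1.960 + 0.842)² / [12 × 0.5 × 0.5 × (p'' − 0.5)²].
- 6 months: N = 36.16, so 19 per arm.
- 12 months: N = 62.26, so 32 per arm.

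Both match the protocol. The formula has no covariate term, so omitting SVC makes no stated number wrong.

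**Step 2: power with SVC added.** Dividing the variance by its unexplained share, power = Φ( √[12c(1−c)N / (1−R²)] × (p'' − 0.5) − 1.960 ). For 46 vs 46, N = 92 and √(3 × 92) = 16.61. At p'' = 0.705 and R² = 0 this is Φ(16.61 × 0.205 − 1.960) = Φ(1.446) = 92.6%. At R² = 0.10 it is Φ(3.406/0.949 − 1.960) = Φ(1.630) = 94.8%.

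| Comparison | R²=0 | 0.02 | 0.05 | 0.10 |
|---|---|---|---|---|
| 12 months, 46 vs 46, p''=0.705 | 92.6% | 93.1% | 93.8% | 94.8% |
| 12 months, 39 vs 39 (15% loss), p''=0.705 | 88.0% | 88.6% | 89.6% | 91.1% |
| 12 months, 46 vs 46, p''=0.65 (assumed) | 70.3% | 71.1% | 72.5% | 74.8% |
| 6 months, 23 vs 46, p''=0.769 | 95.4% | 95.8% | 96.3% | 97.0% |

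**Step 3: what the R² = 0 column leaves out.** It is the unadjusted formula, not the planned ANCOVA. Whatever the planned covariates explain already raises power and leaves less to gain. As an illustration, suppose they explain 20% of the variance. At 39 vs 39, p'' = 0.705, √(3 × 78) × 0.205 = 3.136, and Φ(3.136/√0.80 − 1.960) = 93.9%. Adding SVC with partial R² = 0.04 gives Φ(3.506/√0.96 − 1.960) = 94.7%, a gain of under one point.

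The formula also does not charge for the extra parameter. A two-arm fit on 92 patients has an intercept, treatment, two continuous and two binary covariates, leaving 86 residual degrees of freedom, or 85 with SVC. A useless covariate inflates the variance by roughly 1/85, about 1.2%. That lowers the 92.6% by about 0.3 points and the 70.3% by about 0.5 points.

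**Step 4: which R² is plausible.** A simulation with assumed inputs gave SVC a latent correlation of 0.3 to 0.5 with survival and varied its correlation with functional change among survivors. The resulting R² with the joint rank was:

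| Share of deaths (assumed) | SVC predicts deaths only | Also correlated 0.1 with function | Also correlated 0.3 with function |
|---|---|---|---|
| 5% | 0.003–0.008 | 0.021–0.029 | 0.098–0.119 |
| 10% | 0.008–0.024 | 0.027–0.053 | 0.103–0.142 |
| 20% | 0.023–0.063 | 0.045–0.095 | 0.109–0.178 |

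Through deaths alone the contribution is small. An R² near 0.10 generally needs SVC also to predict functional decline beyond baseline ALSFRS-R and progression rate. The range 0 to 0.10 is therefore a reasonable span, and higher values are optimistic.

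**The case against.** The strongest reply is that nothing here is wrong. The covariate list is prespecified, agrees between Table 1 and item 20a, and already holds baseline function, pre-treatment slope and ALS type. Randomisation protects the type I error with or without SVC, and a case could be made for many other prognostic variables. All of that stands, and it is why the point is an improvement only.

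A reader might infer more: that the plan gives up substantial precision at no cost, because respiratory deaths dominate the low ranks and SVC varies widely at entry. The documents do not support this.
- They give no expected number of deaths at 6 or 12 months.
- They give no SVC distribution. No SVC threshold is listed, but entry is limited to ALSFRS-R 31 to 46, to intermediate progressors and to under two years from diagnosis, and tracheostomy and most ventilator use are excluded.
- They give no correlation between SVC and the joint rank.
- The change is not free. Missing or unreliable baseline SVC needs a rule, and item 25 requires IRB and regulatory approval for most protocol revisions.

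The timing of the covariate is also a fair objection. Item 33 puts randomisation before bone marrow collection, and item 11a puts that collection 36 days before the first injection. A last value before first dosing may therefore fall after randomisation, and may be missing for patients in the ITT set who are never dosed. This changes the fix but does not remove the point: SVC differs from an arbitrary extra variable because it is already collected and the protocol itself gives reasons to think it prognostic.

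**Conclusion.** The point holds as an optional efficiency improvement. Baseline SVC is absent from the primary and matching secondary ANCOVAs, it is collected anyway, and adjusting for it would be valid if fixed in advance. The plan is not in error, and neither its sample size nor its type I error control is affected.

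The size is unknown from the documents. Under an assumed partial R² of 0 to 0.10 and the unadjusted formula at 46 vs 46, power on the 12-month gatekeeping test rises by about 0 to 2 points from 92.6% at the planning effect, and by about 0 to 4.5 points from 70.3% if the true p'' were 0.65 (an assumed value). If SVC adds nothing, the expected loss is a fraction of a point. The case rests on that asymmetry, not on any demonstrated loss.

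**What to change.** Before unblinding, add baseline SVC as one continuous covariate to the two primary joint-rank ANCOVAs and to the secondary ANCOVAs for joint rank and ALSFRS-R change, in Table 1 and item 20a. Define it as the last value before randomisation. If the visit schedule has none, use the trial's own blinded pre-dose baseline. Fill missing baseline values by a simple imputation that ignores treatment group, so that every ITT subject stays in, and state in advance how a measurement judged unreliable is treated.

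The cost is one degree of freedom, the handling rule, and an amendment to the protocol and analysis plan with the approvals that item 25 requires. No new data collection is needed if a suitable baseline value is already scheduled.
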